**2.3.6.6 Outcome measures**

**Primary outcomes**
•Carotid artery and superficial femoral artery diameter, PSV, EDV, RI, and endothelial shear stress (Doppler ultrasonography).•Regional grey matter volume and TIV (T1-weighted VBM).•FA, MD, RD, and AD of major white matter tracts (DTI).•Resting-state functional connectivity of the DMN, FPN, and SN (rs-fMRI).

**Secondary outcomes**
•Eriksen Flanker task: mean reaction time and accuracy for congruent and incongruent conditions; flanker interference effect.•N-Back task: d-prime and median reaction time across 0-Back, 1-Back, 2-Back, and 3-Back conditions.

**2.3.6.7 Statistical analysis**

All statistical analyses will be performed using Jamovi. Demographic and clinical characteristics will be summarised using descriptive statistics: mean ± standard deviation (SD) for normally distributed continuous variables; median and interquartile range (IQR) for skewed data; and frequencies with percentages for categorical variables. Normality will be assessed using the Shapiro-Wilk test. Group differences in neuroimaging and cognitive outcomes will be examined using independent-samples t-tests or Mann-Whitney U tests, as appropriate. A two-way ANOVA will be used to investigate interactions between group and sex or age; a nonparametric alternative (Kruskal-Walli’s test with Dunn’s post hoc correction) will be applied when distributional assumptions are violated. Associations between neuroimaging metrics, vascular parameters, metabolic indices, and cognitive performance will be explored using Pearson’s or Spearman’s correlation coefficients and multiple linear regression models, adjusting for age, sex, years of education, and physical activity level. A significance threshold of p < 0.05 (two-tailed) will be applied throughout.

### 2.4 Phase 2

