**Methods:**

This three-phase, prospective protocol will be conducted at Kasturba Hospital and the Center for Integrative Medicine and Research, Manipal Academy of Higher Education, Manipal, India. Phase 1 is a case-control study (n = 80; 40 obese-diabetic, 40 obese-non-diabetic; age 60–80 years) employing carotid Doppler ultrasonography, T1-weighted voxel-based morphometry and region-of-interest segmentation (SPM12/CAT12/AAL3), diffusion tensor imaging with ROI-based tractography (ExploreDTI), and resting-state fMRI (CONN toolbox), alongside the Eriksen Flanker and N-Back cognitive tasks. Phase 2 involves the systematic development and expert content-validation of a structured, AYUSH-compliant yoga module tailored for elderly obese-diabetic adults. Phase 3 applies the validated module in a 6-month pre-post intervention, with objective adherence monitoring via triaxial accelerometry and repeat of the full Phase 1 neuroimaging and cognitive battery.

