**Sequence 1: Structural MRI — Volumetric brain morphometry**

A T1-weighted three-dimensional Fast Spoiled Gradient Echo (FSPGR) sequence will be acquired for voxel-based morphometry (VBM) analysis. Imaging parameters will include repetition time (TR) = 7.8 ms; echo time (TE) = 3.1 ms; inversion time (TI) = 1010 ms; flip angle = 10°; field of view (FOV) = 256 × 256 mm; voxel size = 1 × 1 × 1 mm isotropic; 176 contiguous axial slices. Post-processing and analysis will be performed in MATLAB (MathWorks) using the SPM12 toolbox (Wellcome Centre for Human Neuroimaging, UCL) with the CAT12 (Computational Anatomy Toolbox, version 12) extension.
^
28
^ The standard CAT12 cross-sectional pipeline will be applied, comprising: (1) bias-field correction and denoising; (2) unified segmentation into grey matter (GM), white matter (WM), and cerebrospinal fluid (CSF) tissue classes; (3) diffeomorphic registration to the MNI152 standard space using the Geodesic Shooting algorithm (DARTEL); and (4) modulation of segmented images to preserve absolute tissue volumes following normalisation. For ROI-based segmentation, the CAT12 automated parcellation will be applied using the Automated Anatomical Labeling (AAL3) atlas, extracting absolute and relative grey matter volumes for bilateral regions of interest, including the hippocampus, entorhinal cortex, prefrontal cortex, anterior cingulate cortex, insula, and parietal association cortex. Total intracranial volume (TIV) will be extracted from the Jacobian determinant maps and used as a covariate in all volumetric analyses to account for individual differences in head size.

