**Sequence 3: Resting-State functional MRI (rs-fMRI)**

Resting-state BOLD (Blood Oxygenation Level-Dependent) fMRI will be acquired using a gradient-echo echo-planar imaging (EPI) sequence. Parameters: TR = 3000 ms; TE = 30 ms; flip angle = 80°; FOV = 230 × 230 mm; voxel size = 3.5 × 3.5 × 3.5 mm; 40 interleaved axial slices. Participants will be instructed to lie still with eyes open, fixated on a cross projected on a screen, and to refrain from deliberate mental activity. RS-fMRI data will be preprocessed using the CONN toolbox (v22.a) in MATLAB, including slice-timing correction, realignment, co-registration to T1 structural image, normalization to MNI space, and spatial smoothing (6 mm FWHM Gaussian kernel).
^
30
^ Independent component analysis (ICA) will be used to identify and remove noise components (motion, physiological artifacts). Default mode network (DMN), frontoparietal network (FPN), and salience network (SN) connectivity will be examined as primary functional outcomes using seed-based and ICA-based approaches.

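### The rule placing all statistics in Jamovi at p < 0.05 conflicts with the SPM12 assignment for VBM and leaves the primary connectivity outcome with no defined per-person value

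*Protocol article*

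**What the plan says.** Section 2.3.6.7 (Phase 1 statistical analysis) fixes three things:

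- Software: "All statistical analyses will be performed using Jamovi".
- Test for imaging outcomes: "Group differences in neuroimaging and cognitive outcomes will be examined using independent-samples t-tests or Mann-Whitney U tests, as appropriate".
- Threshold: "A significance threshold of p < 0.05 (two-tailed) will be applied throughout".

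The only correction it names belongs to the nonparametric fallback for the two-way ANOVA: "test with Dunn’s post hoc correction) will be applied when distributional assumptions are violated".

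Section 2.3.6.4 reads differently:

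- Sequence 1 (T1): the "sequence will be acquired for voxel-based morphometry (VBM) analysis", and "Post-processing and analysis will be performed in MATLAB (MathWorks) using the SPM12 toolbox" with the CAT12 extension. The same paragraph then describes extraction of volumes for named bilateral AAL3 regions, and requires total intracranial volume (TIV) as a covariate in volumetric analyses. The abstract's Methods list "T1-weighted voxel-based morphometry and region-of-interest segmentation".
- Sequence 2 (DTI): each metric is reduced to one mean per tract for each person.
- Sequence 3 (rs-fMRI): connectivity of the three networks is examined "as primary functional outcomes using seed-based and ICA-based approaches". CONN is named for preprocessing only, and no summary value is defined.

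Section 2.5.10 (Phase 3) compares imaging outcomes before and after yoga by paired t-tests or Wilcoxon tests, adds mixed models, and states no map-level rule.

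**The concern.** The tests in section 2.3.6.7 each take one number per participant, whereas VBM and seed-to-voxel analyses commonly produce a test at every voxel. Two consequences follow.

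First, the article gives two homes to the T1 analysis (SPM12/CAT12 and Jamovi), and the word *all* leaves no room for both.

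Second, one primary outcome family, connectivity, has neither a defined number to enter into the stated tests nor a rule for inference on a map.

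The choice between a network average and a map, and the threshold for that map, therefore stays open until the data are seen. A chance cluster could then be reported as atrophy or dysconnectivity in Phase 1, or as a yoga effect in Phase 3. This differs from testing many named outcomes: adjusting across outcomes does not control error within a single voxelwise map.

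**Working it through.** **Step 1. Which primary imaging outcomes have a value that the stated tests can use?**

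| Outcome family (2.3.6.6) | Per-person value defined? | Software named in 2.3.6.4 | Fits 2.3.6.7? |
|---|---|---|---|
| Regional grey matter volume, TIV | Yes: AAL3 regional volumes | MATLAB, SPM12/CAT12, including analysis | Yes for regional volumes; no for a voxelwise map |
| FA, MD, RD, AD by tract | Yes: tract means | ExploreDTI | Yes |
| DMN, FPN, SN connectivity | No | CONN, preprocessing only | Not until a value is defined |

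The Doppler measures, also primary, are single values and are not affected. The gap therefore has two parts: a software conflict for VBM, and a missing definition for connectivity.

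**Step 2. What would the blanket threshold do if a map were read at it?**

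The article gives no figure for this, so there is nothing to reproduce. Inputs: voxel size 3.5 × 3.5 × 3.5 mm (Sequence 3), threshold 0.05 (section 2.3.6.7), and a brain volume of 1.2 to 1.4 L (my assumption; not in the article).

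- Voxel volume: 3.5³ = 42.875 mm³.
- Voxels: 1,200,000 / 42.875 = 27,988, up to 1,400,000 / 42.875 = 32,653.
- Expected false positives with no effect: 0.05 × 27,988 = 1,399, up to 0.05 × 32,653 = 1,633.

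A second route starts from the acquisition grid. (230 / 3.5)² × 40 ≈ 172,735 voxels. If 10% to 30% of the grid is tested (also assumed), that is 17,273 to 51,820 voxels, with 864 to 2,591 false positives expected.

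The 5% proportion does not depend on either assumption or on spatial smoothing; only the count does. The counts are at acquisition resolution and would change if the images were resampled.

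**Step 3. Could a later analysis plan settle this silently?**

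A plan that added cluster-level control in SPM12 or CONN would contradict both the sentence assigning all analyses to Jamovi and the sentence applying 0.05 throughout. Those sentences have to change in either case.

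**The case against.** The strongest reply is that section 2.3.6.7 was written for extracted values. Every test there takes one number per person, section 2.3.6.6 words the structural outcome as regional volume, and the Discussion describes VBM with ROI segmentation as if it were one pipeline. On this reading Jamovi is workable and SPM12 is the route to the numbers. This largely stands for grey matter and wholly for the tracts.

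A reader might infer more: that the imaging analyses cannot be run at all, that two primary imaging families have no valid test, or that the investigators plan to read maps at an uncorrected 0.05. The article supports none of these. Regional volumes and tract means give an executable route. Sequence 3 speaks of approaches, not of maps, and seed-based connectivity between network regions can yield one value per person. No voxel threshold appears anywhere.

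It is also fair to say that cluster thresholds are usually left to an analysis plan or full protocol, so their absence alone would be no finding.

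Two things survive. Sequence 1 assigns analysis, not only processing, to SPM12, against an unqualified *all* in section 2.3.6.7. And Sequence 3 calls connectivity primary without the per-person summary that Sequence 2 supplies for tracts. Both concern what the article states.

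**Conclusion.** The point holds in a limited form. The software and threshold sentences in section 2.3.6.7 conflict with the SPM12/CAT12 assignment for VBM, and they do not fit a connectivity outcome that has no defined value. Regional volumes, tract means and Doppler measures are unaffected by this point.

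If a voxelwise map were read at the blanket 0.05, about 5% of its voxels would be false positives under the null, roughly 1,400 to 1,630 at 3.5 mm for an assumed 1.2 to 1.4 L brain. That measures what the present wording would allow, not an analysis the article proposes. The conclusion rests on the wording of the sections and on the stated tests needing one value per person.

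It should be corrected before data collection. The Data Availability section says that no participant data had been collected at publication.

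**What to change.** 1. Limit the Jamovi sentence and the plain 0.05 rule to extracted per-person values: regional volumes, tract means, and one prespecified connectivity value for each of DMN, FPN and SN. Define that value in Sequence 3.
2. State that any voxelwise VBM map is tested in SPM12/CAT12, and any seed-to-voxel or ICA map in CONN, by a general linear model (with TIV for VBM), at cluster-level familywise p < 0.05 with a fixed cluster-forming threshold.
3. State before data collection whether the per-person value or the map is the primary reading.
4. Apply the same rules to the pre-post comparisons in section 2.5.10.

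This takes a few sentences and uses software already named. The downside is that fewer map-level findings will reach significance.

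It does not settle multiplicity across the per-person outcomes, which is a separate matter. With 12 bilateral regions (6 × 2), 24 tract metrics (6 × 4) and 3 network values, 39 independent tests at 0.05 would give a familywise error of 1 − 0.95³⁹ = 0.86. Correlation among the outcomes would lower this.

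### Phase 1 compares the groups without covariates, which conflicts with the TIV rule for grey matter volume and leaves the other outcomes unadjusted; the Kruskal-Wallis fallback cannot test an interaction

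*Protocol article*

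**What the plan says.** Section 2.3.6.7 (Statistical analysis, Phase 1) gives three rules that matter here.

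- Group contrast: "Group differences in neuroimaging and cognitive outcomes will be examined using independent-samples t-tests or Mann-Whitney U tests, as appropriate".
- Interactions: "A two-way ANOVA will be used to investigate interactions between group and sex or age". The nonparametric substitute, Kruskal-Wallis with Dunn's post hoc correction, "will be applied when distributional assumptions are violated".
- Adjustment: the only adjusted models in the section relate imaging, vascular, metabolic and cognitive measures to one another. They are described as "multiple linear regression models, adjusting for age, sex, years of education, and physical activity level". These adjusters belong to the association analyses. They are not assigned to the group contrast, and TIV is not among them.

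Section 2.3.6.4, Sequence 1 (structural MRI), says that TIV will be "used as a covariate in all volumetric analyses to account for individual differences in head size". Section 2.3.6.6 lists among the primary outcomes "Regional grey matter volume and TIV (T1-weighted VBM)".

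Phase 1 is a case-control study (2.3.2) of people aged 60 to 80 of both sexes (2.3.3), with 40 per group (2.3.5). None of these sections states matching or balancing of the groups.

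**The concern.** A two-sample t-test or a Mann-Whitney test has no place for a covariate, so an analyst cannot obey both 2.3.6.7 and the TIV rule for grey matter volume. The two instructions can give different answers for a primary outcome, and the choice would be made after the data are seen.

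For diffusion, connectivity, Doppler and cognitive outcomes there is no such contradiction. The difficulty is that the groups are formed by disease status, not by randomisation. A difference in age, sex or education can therefore appear as a difference due to diabetes. The authors evidently regard these variables as relevant, since they adjust the exploratory models for them, yet the main comparison goes without.

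Kruskal-Wallis compares several groups along one classification and contains no interaction term. As a substitute for a two-way ANOVA aimed at interactions, it answers a different question.

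**Working it through.** **1. The rules side by side for regional grey matter volume.**

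| Source | Instruction | Takes a covariate? |
|---|---|---|
| 2.3.6.4, Sequence 1 | TIV is a covariate in all volumetric analyses | Required |
| 2.3.6.7, group differences | t-test or Mann-Whitney | No |
| 2.3.6.7, two-way ANOVA | group with sex or age, for interactions | Sex or age only; not TIV or education |
| 2.3.6.7, association models | age, sex, education, physical activity | Yes, but not TIV and not for the group contrast |

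No analysis named in 2.3.6.7 gives a TIV-adjusted group difference.

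**2. Size of confounding (illustration).** The plan gives no figure for this, so the inputs are assumptions: a covariate correlates r with the outcome within groups, the groups differ by δ SD on it, and diabetes has no true effect. The apparent effect is d = r × δ. With n = 40 per group, the noncentrality is d × √(n/2) = 4.472 d on 78 degrees of freedom, two-sided 5%.

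| r | δ | Apparent d | Noncentrality | Rejection rate |
|---|---|---|---|---|
| 0.3 | 0.3 | 0.09 | 0.40 | 6.8% |
| 0.3 | 0.5 | 0.15 | 0.67 | 10.2% |
| 0.5 | 0.3 | 0.15 | 0.67 | 10.2% |
| 0.5 | 0.5 | 0.25 | 1.12 | 19.7% |

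The nominal rate is 5%.

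**3. Precision lost (illustration, same r, no imbalance).** Adjustment shrinks the residual SD by √(1 − r²), so a true d = 0.5 acts like 0.5/√(1 − r²).

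- Unadjusted: d = 0.5, power 0.60.
- r = 0.3: 0.5/√0.91 = 0.524, power 0.64.
- r = 0.5: 0.5/√0.75 = 0.577, power 0.72.

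**4. Kruskal-Wallis in place of the interaction test.** Simulation with normal data, 20 per group-by-sex cell (80 in all) and 5% level. The 0.5 SD and ±0.5 SD rows were run separately from the others and without the ANOVA comparison. A crossover of ±0.4 SD means cell means of +0.4, −0.4, −0.4 and +0.4.

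| Truth | Kruskal-Wallis, four cells | Kruskal-Wallis, by group | ANOVA interaction |
|---|---|---|---|
| No effects | 5.1% | 5.2% | 4.9% |
| Sex effect 0.5 SD, no interaction | about 40% | – | – |
| Sex effect 0.8 SD, no interaction | 82% | 3.2% | 5.0% |
| Crossover ±0.4 SD | 83% | 3.6% | 94% |
| Crossover ±0.5 SD | – | about 3% | – |

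On four cells the test rejects about equally often for a plain sex effect (82%) and for a true interaction (83%), so it cannot tell them apart. By group alone it does not see the interaction. The ANOVA interaction test keeps its 5% level and finds the ±0.4 SD crossover in 94% of runs.

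**The case against.** Several points on the other side carry weight.

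- **Scope of the TIV rule.** It governs volumes only. A reader might infer that the whole Phase 1 analysis contradicts it. The document does not support that: diffusion, connectivity, Doppler and cognitive outcomes fall outside the rule.
- **The volumes may already be corrected.** Sequence 1 extracts relative as well as absolute volumes and places the T1 analysis in SPM12/CAT12, where a TIV-adjusted model may be intended. This softens the conflict but does not remove it. What the volumes are relative to is not defined, a ratio is not a covariate, absolute volumes are extracted too, and 2.3.6.7 assigns all statistical analyses to Jamovi.
- **Matching.** A reader might infer that the groups are known to be unmatched. The article is only silent, and the full protocol may say more. The point is that no matching is stated and the named test does not adjust.
- **Age and sex are not ignored.** It would be too strong to say that any imbalance will be read as a diabetes effect. The two-way ANOVA also yields a group effect alongside sex or age. It is specified for interactions, however, and leaves out education and TIV.
- **Power.** A gain to 0.88 can be calculated, but it needs covariates that explain half of the variance. Correlations of 0.3 to 0.5 give 0.64 to 0.72.
- **Interpretation.** A reader might infer that a significant Kruskal-Wallis result will be reported as effect modification. The plan does not say how the result would be read. What stands is that the test cannot answer the question assigned to it.

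**Conclusion.** The point holds in three parts of different weight. First, 2.3.6.7 and the TIV rule cannot both be followed for regional grey matter volume, a primary outcome; this needs no numerical assumption. Second, the remaining imaging and cognitive contrasts are unadjusted in a non-randomised comparison, although the plan names suitable adjusters elsewhere. The size of this depends on assumed correlations and imbalances that no figure in the document supports: about 7% to 20% false positives instead of 5%, or, with no imbalance, power of 0.60 where 0.64 to 0.72 was available. Third, Kruskal-Wallis is the wrong fallback for an interaction. That is a method error whatever the data; the simulated rates only show its size, and it affects the interaction analyses alone.

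**What to change.** Rewrite the group-comparison and interaction sentences of 2.3.6.7 as follows.

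- Make the primary group comparison a linear model (ANCOVA) for each outcome with group, age, sex and years of education. Add TIV for every regional volume, but not when TIV is itself the outcome, since it cannot be adjusted for itself.
- Add physical activity in a sensitivity analysis, because diabetes may affect it and conditioning on it could remove part of the contrast. BMI is optional.
- Report adjusted differences with 95% confidence intervals, using robust or bootstrap standard errors when residuals are non-normal.
- Test group-by-sex and group-by-age interactions in the same model, with age continuous, and delete the Kruskal-Wallis fallback.
- Keep the t-tests and Mann-Whitney tests as descriptive.

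The cost is wording and a few degrees of freedom out of 80 participants. The adjusters are already named in the plan, and TIV is already extracted. The Data Availability statement says that no participant data had been collected at publication, so at that point the change could still be pre-specified.

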**2.3.3 Inclusion criteria**
•Age 60–80 years, both sexes.•Clinical diagnosis of type 2 diabetes mellitus for the obese-diabetic group.•Body mass index (BMI) ≥ 25 kg/m
^2^ as per Asia-Pacific guidelines for obesity classification.
^
25
^
•Able to provide written informed consent independently or through a legally authorized representative.

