**2.3.5 Sample size**

Sample size was estimated using G*Power 3.1 software. A multivariate analysis of variance (MANOVA) power analysis was performed with an assumed medium effect size (f
^2^ = 0.25), a significance level of α = 0.05, and a desired statistical power of 0.80. This yielded a minimum total sample of 80 participants. Accounting for anticipated attrition and protocol deviations, 40 participants will be recruited to each group (obese-diabetic and obese-non-diabetic), yielding a total of 80 participants for Phase 1.

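### The two-way ANOVA named for the Phase 1 group-by-age interaction implies banding age, which costs power against a continuous-age term, and its rank-based fallback does not test an interaction

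*Protocol article*

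**What the plan says.** In the protocol article, section 2.3.6.7 (Statistical analysis, Phase 1), the sentence on effect modification reads "A two-way ANOVA will be used to investigate interactions between group and sex or age". If assumptions fail, the same sentence turns to the Kruskal-Wallis "test with Dunn’s post hoc correction) will be applied when distributional assumptions are violated". The next sentence plans "multiple linear regression models, adjusting for age, sex, years of education, and physical activity level". Those regressions concern associations among imaging, vascular, metabolic and cognitive measures, and no product of group and age is named in them. The section closes with "A significance threshold of p < 0.05 (two-tailed) will be applied throughout".

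The inclusion criteria (2.3.3) give "Age 60–80 years, both sexes". The sample size section (2.3.5) states "40 participants will be recruited to each group (obese-diabetic and obese-non-diabetic), yielding a total of 80 participants for Phase 1". No age bands, age distribution, interaction effect size or interaction power appear anywhere in the article.

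**The concern.** A two-way ANOVA crosses two categorical factors. Sex is one; age over a 20-year range is not, unless it is grouped. Three features of the text point to grouping:

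- Sex and age are offered as interchangeable second factors.
- The fallback works only on discrete groups.
- Where age is meant as a covariate, the article uses the word regression.

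Grouping treats everyone in a band as the same age. Any age gradient inside the band then moves into the error term, and each band beyond two spends a further numerator degree of freedom. If the diabetic versus non-diabetic difference really changes with age, it is more likely to be missed. This ANOVA is the only Phase 1 test of that question that the article names.

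The fallback has a separate fault. Kruskal-Wallis is a one-way test of whether several groups share a distribution. Applied to the cells of a group-by-sex or group-by-age-band table, it mixes both main effects with the interaction and cannot isolate the interaction. Dunn's pairwise comparisons do not repair this.

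**Working it through.** **The plan's own figure.** The article gives no power for the interaction. Its stated figure is a total of 80 from a different calculation: "A multivariate analysis of variance (MANOVA) power analysis was performed with an assumed medium effect size", with f² = 0.25, alpha 0.05 and power 0.80. For a two-group MANOVA with p responses (numerator df p, denominator df N − p − 1, noncentrality f²N), the required N is 34 at p = 1, 78 at p = 11 and 81 at p = 12. The number of responses is not stated, so 80 can be neither confirmed nor refuted. Either way, its 80% power is not power for group by age.

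**Inputs for the check.** From the article: N = 80, 40 per group, two-sided alpha 0.05. Assumed: a linear change of the group difference with age, the same age distribution in both groups (uniform or normal), K equal-sized bands with K = 2, 3 or 4, and a reference power for the continuous-age test.

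**Formulas.**

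- Continuous age: F test of one product term on 1 and 76 df, critical value 3.97, noncentrality λ.
- Banded age: F test on K − 1 and 80 − 2K df, noncentrality λ × R. R is the between-band share of the age variance.
- For uniform age, R = 1 − 1/K², which gives 0.75, 0.89 and 0.94. For normal age, R = 0.64, 0.79 and 0.86.

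**Numbers at 80% reference power.** This requires λ = 8.05. Since λ = (40/2) × δ², where δ is the slope difference in outcome SDs per SD of age, δ = √(8.05/20) = 0.63.

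- Uniform age, 2 bands: λR = 8.05 × 0.75 = 6.04, power 68.0%, loss 12.0 points.
- Uniform age, 3 bands: λR = 8.05 × 0.889 = 7.16, power 64.7%, loss 15.3 points.
- Normal age, 2 bands: λR = 8.05 × 0.637 = 5.13, power 60.9%, loss 19.1 points.
- Normal age, 3 bands: λR = 8.05 × 0.793 = 6.39, power 59.4%, loss 20.6 points.

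**Loss in percentage points at other reference powers.**

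| Power with continuous age | Uniform, 2 / 3 / 4 bands | Normal, 2 / 3 / 4 bands |
|---|---|---|
| 30% | 6.3 / 9.3 / 11.8 | 9.2 / 11.2 / 13.0 |
| 50% | 10.3 / 14.4 / 18.3 | 15.4 / 17.8 / 20.7 |
| 70% | 12.4 / 16.3 / 21.0 | 19.1 / 21.2 / 24.6 |
| 80% | 12.0 / 15.3 / 20.0 | 19.1 / 20.6 / 24.1 |
| 95% | 7.3 / 8.5 / 11.5 | 13.0 / 12.9 / 15.1 |
| 99% | 3.0 / 3.2 / 4.5 | 6.2 / 5.6 / 6.6 |

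Taking the MANOVA value f² = 0.25 literally for the interaction would give λ = 0.25 × 80 = 20 and about 99% power, close to the last row.

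**Simulation check.** With uniform, truncated-normal and skewed ages inside 60 to 80, at continuous-age power of about 77 to 79%, the losses were 15.0 to 18.4 points for two bands, 17.8 to 20.2 for three and 22.7 to 24.9 for four. These agree with the formulas to within about 4 points.

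**The case against.** The strongest reply is that the article never says age will be banded. ANOVA is sometimes used loosely for a linear model that includes a covariate, and the shared fallback clause would also fit group-by-sex cells. So the fallback supports banding without proving it. That stands: banding is a strong inference from the named method, not stated text. The absence of a cut point is also not a fault in itself, because a condensed article may leave it to the full protocol or the analysis plan. What remains is that the named method does not suit a continuous age variable, and an analyst who follows the sentence literally would have to band.

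It is also fair to say that the size of the loss is not a property of this plan. The 80% reference is borrowed from the MANOVA sizing, and the document does not support the slope difference of 0.63 that it needs. A reader might infer that the plan certainly forfeits some 12 to 22 points, or that banding always discards at least a quarter of the information. Neither holds. The loss shrinks when the true interaction is small or very large. A quarter or more is lost only with two bands: three bands retain 0.79 to 0.89 of the information, and much of their power loss comes from the extra degree of freedom.

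A reader might also take age dependence to be the central Phase 1 question, or this to be the weakest planned test. The Phase 1 objective is a comparison between groups, no interaction is listed among the outcomes, and group by sex is another interaction test in the same 80 people.

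**Conclusion.** The point holds as a conditional one about a subsidiary analysis. Taken literally, the named test requires age bands. For a roughly linear age-by-group effect, banding lost power against continuous age in every scenario examined. The loss is about 12 to 21 points for two or three equal bands if the continuous test had 80% power, and about 3 to 25 points over the wider set of assumptions. These figures rest on assumed linearity, age distribution, number of bands and true effect size, none of which the article gives. The planned t-tests and Mann-Whitney tests between groups are untouched.

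The fault in the fallback needs no such assumptions: Kruskal-Wallis with Dunn's test does not test either interaction.

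**What to change.** In section 2.3.6.7:

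- Keep the two-way ANOVA for group by sex.
- For age, specify a linear model with group, age in years (continuous, mean-centred) and their product, and report the interaction slope with its 95% confidence interval.
- If age bands are wanted for display, fix them in advance and use them for description only.
- Remove Kruskal-Wallis with Dunn's test as the fallback for both interactions. Where distributional assumptions fail, use the same linear model with robust standard errors, or with a transformed or aligned-rank outcome.

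The cost is a sentence or two of wording. No extra participants, data or procedures are needed, and linear modelling is already planned in the same section. The small downside is the assumption that the age effect is linear over 60 to 80 years, which residual plots can check.
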